## Objectives

### Primary objective

To assess the diagnostic accuracy of OCT for paediatric IH.

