### Outcome measures

Our primary outcome measures are OCT examinations and ICP assessments. Our primary OCT outcome measure is retinal nerve fibre layer (RNFL) thickness; other OCT parameters are listed below. OCT examination must be performed at the time of ICP assessment, or within 28 days prior to or 14 days following ICP assessment. Only one visit per child for OCT examination is required to fulfil the primary objective.

Our secondary outcome measures include the following, where possible:

Success rates of handheld OCT in children at risk of IH, particularly in craniosynostosis.Repeated OCT data between clinic visits±ICP assessments±cranial vault expansion surgery±follow up, with repeated ICP data if available.Fundoscopic examination within 3 months of OCT examination and/or at most recent follow-up visit.VA measured within 3 months of OCT examination and/or at most recent follow-up visit.Contrast sensitivity measured within 3 months of OCT examination and/or at most recent follow-up visit.Visual field testing within 3 months of OCT examination and/or at most recent follow-up visit.Visual evoked potentials (VEPs) within 3 months of OCT examination and/or at most recent follow-up visit.Comparison of the above measures with ICP and final VA, where available and appropriate.

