### Sample size calculation

A cohort of at least 39 children is required to demonstrate at least 40% improvement in sensitivity compared with 22% by fundoscopy demonstrated by Tuite *et al*^27^ (McNemar’s Z-test: n=39; power=80%, α=0.05). This would demonstrate sensitivity of at least 62%, a conservative estimate comparable to the least sensitive OCT measure demonstrated by Swanson *et al*^16^ (maximal retinal thickness, 63% sensitivity) for detecting IH in children with craniosynostosis.

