### Statistical analysis

Diagnostic accuracy testing will be performed to calculate sensitivity, specificity, positive predictive value, negative predictive value and accuracy of OCT parameters to detect IH, using the OCT parameters and two definitions of IH described above. Receiver operating characteristic curves will be plotted to evaluate diagnostic accuracy of OCT parameters for IH. Mixed model regression analysis will be performed to assess the strength of association between OCT parameters and secondary outcome measures, described above. The eye recorded (right/left) will be included in the model, to address intereye correlations.

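### The 39 children and 80% power belong to a paired OCT-versus-fundoscopy test that the stated objectives and analyses do not contain

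*Protocol article*

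**What the plan says.** The protocol article's Sample size calculation states that "A cohort of at least 39 children is required" to show "at least 40% improvement in sensitivity compared with 22% by fundoscopy", and gives the basis as McNemar's "Z-test: n=39; power=80%, α=0.05". The 22% is credited to an earlier published study of children with craniosynostosis. The target is 62%, so the 40% is an absolute gain.

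The primary objective is "To assess the diagnostic accuracy of OCT for paediatric IH". It does not mention fundoscopy.

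The Statistical analysis section says "Diagnostic accuracy testing will be performed to calculate sensitivity, specificity, positive predictive value, negative predictive value and accuracy of OCT parameters to detect IH", under two definitions of IH, and adds ROC curves for OCT parameters. The one method it names that links OCT to fundoscopy is this: "Mixed model regression analysis will be performed to assess the strength of association between OCT parameters and secondary outcome measures, described above".

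Fundoscopy appears under Outcome measures in the list that opens "Our secondary outcome measures include the following, where possible". Its window is 3 months around the OCT examination, with the latest follow-up visit as an addition or alternative. The same list ends with a comparison of these measures with ICP and final visual acuity, for which no method is given.

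**The concern.** McNemar's test is a within-child comparison. To compare sensitivities it needs an OCT result and a fundoscopy result in the same child, and it uses only children who have IH on the reference standard. The sizing section rests on that test, but the sections that set out the objectives and analyses do not state it. The comparator it depends on is optional and may be recorded well after the ICP assessment.

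At stake is the study's motivating claim. The Introduction argues from fundoscopy's poor sensitivity to the need for a more sensitive non-invasive measure. If only the listed analyses are run, the report will give OCT accuracy and an association between OCT and fundoscopy, and the 80% power will attach to neither. A reader could then take an informal comparison with the published 22% as the powered result.

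**Working it through.** **Inputs.** From the Sample size calculation: sensitivities 0.22 and 0.62, difference d = 0.40, α = 0.05, power 80%, n = 39. Sidedness and discordance are not stated; two-sided α is assumed.

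**1. Reproduce 39 as a McNemar calculation.** With pd the total proportion of discordant pairs,

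n = [1.96·√pd + 0.842·√(pd − d²)]² / d².

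Taking the discordant cells as 0.62 and 0.22 gives pd = 0.84:

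- n = [1.96·√0.84 + 0.842·√0.68]² / 0.16 = 38.76, rounded up to 39.
- Power at 39 = Φ[(0.40·√39 − 1.96·√0.84)/√0.68] = Φ(0.85) = 80.3%.

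The stated figure is therefore reproduced. Using the two sensitivities themselves as discordant cells means that no child is positive on both tests. That is the largest discordance possible for 22% and 62%, so it is conservative. If the two tests were independent, pd = 0.62·0.78 + 0.22·0.38 = 0.567 and n = 26.

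**2. Does 39 fit the benchmark reading?** Test OCT sensitivity against a fixed 0.22, exact binomial, upper tail 0.025, with true sensitivity 0.62. The smallest n reaching 80% power is 13: reject at 7 or more positives, power 81.5%. So 39 is not the size for that analysis.

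**3. Does 39 fit the listed accuracy analysis?** Estimating sensitivity has precision, not power. The Wald 95% half-width at 62% is 1.96·√(0.62·0.38/n):

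- n = 39 with IH: ± 15.2 points.
- n = 20 with IH (assumed): ± 21.3 points.

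**4. What the paired test would deliver if adopted.** The protocol counts 39 children, not 39 with IH. At pd = 0.84, if 20 had IH and both results (an assumed number, since no IH proportion is given), power = Φ[(0.40·√20 − 1.96·√0.84)/√0.68] = Φ(−0.01) ≈ 50%.

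**5. Set the sections side by side.**

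| Section | Comparison with fundoscopy |
|---|---|
| Sample size calculation | Paired test of sensitivity, 80% power |
| Primary objective | None |
| Statistical analysis | Association by mixed model only |
| Outcome measures | Fundoscopy optional; comparison with ICP, no method named |

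**The case against.** The document is a condensed journal article. Its Sample size calculation already names the test, comparator, α and power, and the Statistical analysis section does not claim to be exhaustive. An unseen analysis plan may hold the paired test. This stands against the stronger inference a reader might draw, that the study will not perform the comparison. The text supports only that the comparison is not stated where the objectives and analyses are set out. The disagreement between sections remains.

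A reader might also infer that fundoscopy has been assigned to an analysis that cannot answer the sized question. That goes too far. Outcome measures plans a comparison of fundoscopy with ICP, which could yield its accuracy in this cohort. The method is unnamed rather than wrong.

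The sizing text compares with a published 22%, so its wording also fits an external benchmark. That is fair, but McNemar's test and 39 are then the wrong test and the wrong number for the purpose, and the passage still needs correcting.

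Finally, the primary objective is OCT accuracy against ICP, and the listed analyses address it directly. No primary estimate becomes wrong. This limits the severity.

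**Conclusion.** The point holds as an inconsistency between sections. The 39 and 80% are arithmetically sound for a two-sided paired test of OCT against fundoscopy sensitivity with maximal discordance, but no objective or listed analysis states that test. Nor do they describe the benchmark reading (about 13 children with IH) or the accuracy estimates (± about 15 points at 62% if all 39 have IH).

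It should be fixed, but it does not invalidate the study, because the OCT accuracy estimates are unaffected. The reproduction assumes two-sided α and discordant cells of 0.62 and 0.22. The figures for 20 children with IH are illustrative, because the protocol gives no expected proportion with IH.

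**What to change.** Align the Sample size calculation and Statistical analysis sections in one of two ways.

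**(a) If a paired comparison is intended,** name it in the objectives and state in the Statistical analysis that, among IH-positive children with both results, the child-level sensitivities of RNFL thickness and fundoscopy will be compared by McNemar's test, with the paired difference and its 95% CI. Also:

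- prespecify which of the two IH definitions applies, the RNFL cut-off, and which fundoscopy grades count as positive;
- use only fundoscopy from a defined window around the ICP assessment, not from a later follow-up visit;
- report the paired difference in specificity in IH-negative children;
- say that 80% power applies only if 39 IH-positive children have both tests (about 50% if 20 do, an assumed number);
- note that, per the Introduction's section on measuring ICP, bolt monitoring is used particularly where ophthalmological findings, including fundoscopy, are equivocal, so fundoscopy's sensitivity may be understated and the comparison may favour OCT.

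**(b) If no paired test is intended,** delete the McNemar and 80% statement and restate 39 as a precision figure for OCT sensitivity: 62% ± about 15 points if all 39 have IH, ± about 21 points if 20 do.

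Either route costs a few sentences and a less favourable stated figure. Fundoscopy is already collected and graded, so no patients or procedures need be added. Route (a) may leave fewer children in the comparison because of the tighter window.

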### Statistical analysis

Diagnostic accuracy testing will be performed to calculate sensitivity, specificity, positive predictive value, negative predictive value and accuracy of OCT parameters to detect IH, using the OCT parameters and two definitions of IH described above. Receiver operating characteristic curves will be plotted to evaluate diagnostic accuracy of OCT parameters for IH. Mixed model regression analysis will be performed to assess the strength of association between OCT parameters and secondary outcome measures, described above. The eye recorded (right/left) will be included in the model, to address intereye correlations.

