### Handheld OCT

OCT has revolutionised the clinical practice of ophthalmology over the past two decades. However, infants and young children have previously been largely deprived of this technology as conventional OCT machines were designed for adults, requiring compliance with a chin rest, good fixation and cooperation. These limitations have been overcome with the recent advent of the handheld spectral-domain OCT designed for infants, which is demonstrably reliable in awake infants.^30 36^ Normal development of the optic nerve^37^ and retina^38^ in children has recently been described using handheld OCT. A wide range of conditions have also been investigated using handheld OCT in children, including retinopathy of prematurity,^39^ nystagmus,^40^ foveal hypoplasia,^41^ optic nerve hypoplasia,^41^ achromatopsia,^42^ albinism,^43^ primary congenital glaucoma,^44^ microcephaly,^45^ craniopagus twins^46^ and others.

More recently, we performed a feasibility and repeatability study^47^ using handheld OCT in children with craniosynostosis (n=50, median age 51 months, age range 2–157 months). We found good feasibility, with 86% achieving at least unilateral OCT and 76% achieving bilateral OCTs of the ONH. This was higher than the success rate in healthy children found by Patel *et al*^37^ (70% achieving at least unilateral OCT imaging of the ONH). Factors boosting the likelihood of success in children with craniosynostosis included good understanding and cooperation of the child and parent/guardian and availability of an assistant. We also performed repeatability analysis in 20 children and found good repeatability (intraclass correlation coefficient range, 0.77–0.99; the majority exceeded 0.90).

Advantages of using handheld OCT in children at risk of IH include the following:

Handheld OCT can be performed in awake babies and infants, without the need for general anaesthesia.Even if under general anaesthesia, handheld OCT can be performed in a child lying down, both in the supine and lateral decubitus positions.Handheld OCT scans can be easily repeated in the clinical setting, enabling the assessment of evolving changes over time.Handheld OCT semiautomated segmentation parameters can be fully controlled by the investigator.^37 38 47^

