### Handheld OCT image acquisition and analysis

A non-contact, spectral domain handheld OCT scanner (Envisu C-2300, 3.3 µm axial resolution; Leica Microsystems, Wetzlar, Germany) will be used to scan the ONH and fovea. A 12×8 mm scanning window will be used in the acquisition protocol—this permits imaging of both the ONH and fovea in one scan. The three-dimensional raster scan for both scan sequences will consist of 100 B-scans and 500 A-scans per B-scan line resulting in a short acquisition time (1.9 s) enabling imaging of the ONH and fovea with minimal movement artefact. Handheld OCT will be performed at the time of 48-hour ICP monitoring to fulfil our primary objective; wherever possible, handheld OCT will also be performed during clinic visits to fulfil our secondary objectives. In awake children, visual devices including cartoons on smartphones and tablets will be used as appropriate. Where possible, an assistant can operate the controls to acquire images, otherwise the lead investigator ([name]) will acquire images alone using the foot pedal.

Our imaging protocol involves scanning the right eye followed by the left eye. Once the image is acquired, the en face view is used to identify the ONH, which is navigated frame by frame until the central slice featuring the deepest optic cup is identified for ONH analysis. For foveal segmentation, the fovea is navigated frame by frame until the central slice featuring the deepest foveal pit is identified. Scans are repeated twice per eye where possible, and any scans of non-analysable quality are discarded. Analysable quality is defined as an ONH tomogram wherein the edges of the disc margins and the cup profile, including its lowermost point, can be clearly visualised, or a foveal tomogram wherein it is possible to identify the foveal pit in full and all foveal layers from the external limiting membrane to Bruch’s membrane. In cases of papilloedema, the handheld OCT probe can be repositioned slightly forwards in the axial plane, or the reference arm can be lowered, until the entire swollen ONH is visualised without missing the disc margins. Using this technique, all cases with papilloedema were successfully imaged in our recent feasibility and repeatability study.^47^

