### ICP assessment

As per standard clinical care at GOSH, patients are admitted for gold-standard, 48-hour ICP assessments. An intraparenchymal catheter and bolt system is used (RAUMEDIC Neurovent-P, RAUMEDIC AG, Helmbrechts, Germany). The neurosurgeon measuring ICP will be masked to the OCT findings. Due to lack of agreement over what ICP values constitute IH in children, two definitions will be used for IH:

Definition 1: Grand mean ICP >15 mmHg, or ICP traces with >2 ICP spikes at least double the baseline ICP and >15 mm Hg for >5 min.Definition 2: Grand mean ICP >20 mmHg, or ICP traces with >2 ICP spikes at least double the baseline ICP and >20 mm Hg for >5 min.

ICP assessments using both definitions will be included in multilevel statistical analyses.

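### A right/left eye term does not address inter-eye correlation, and the protocol names no grouping by child to do so

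*Protocol article*

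**What the plan says.** All references are to the protocol article.

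- **Statistical analysis**, primary: "Diagnostic accuracy testing will be performed to calculate sensitivity, specificity, positive predictive value, negative predictive value and accuracy of OCT parameters to detect IH", with ROC curves to follow. The section does not say whether the unit is the eye or the child.
- **Statistical analysis**, secondary: "Mixed model regression analysis will be performed to assess the strength of association between OCT parameters and secondary outcome measures, described above". The next sentence is the one at issue: "The eye recorded (right/left) will be included in the model, to address intereye correlations". By its position, the model it refers to is this mixed model.
- **ICP assessment**: "patients are admitted for gold-standard, 48-hour ICP assessments", so the reference result belongs to the child. The section adds: "ICP assessments using both definitions will be included in multilevel statistical analyses". The levels are not named.
- **Handheld OCT image acquisition and analysis**: "Our imaging protocol involves scanning the right eye followed by the left eye". Both eyes are therefore measured.
- **Sample size calculation**: the requirement of at least 39 is counted in children.
- **Introduction, Handheld OCT**: in the feasibility study of 50 children with craniosynostosis, "We found good feasibility, with 86% achieving at least unilateral OCT and 76% achieving bilateral OCTs of the ONH".

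**The concern.** The plan names a device and the job it is to do, and the device cannot do that job. Inter-eye correlation means that two eyes of the same child resemble each other more than eyes of different children. A right/left term adds one constant for laterality, the same for every child, so it carries no information about which eyes belong together. Handling the correlation needs a child-level random effect, standard errors clustered by child, or one value per child.

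If an analyst took the sentence at its word and relied on the laterality term alone, each child's two eyes would count as nearly independent observations. Standard errors for child-level associations would be too small and false-positive associations too frequent.

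The primary objective is exposed in a weaker sense. Two eyes are scanned and share one ICP result, and the only sentence on inter-eye correlation concerns a different model. An analyst who pooled eyes for sensitivity, specificity or AUC would find nothing in the article to stop it.

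**Working it through.** **1. The plan's own figure, and its unit.** Inputs from Sample size calculation: sensitivity 22% against 62%, power 80%, α 0.05, McNemar's Z-test. Taking two-sided α and discordant proportions p10 = 0.62 and p01 = 0.22 (no child positive on both tests):

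n = [1.96·√(p10+p01) + 0.8416·√(p10+p01−(p10−p01)²)]² / (p10−p01)²
= [1.96·√0.84 + 0.8416·√0.68]² / 0.16 = (1.796 + 0.694)² / 0.16 = 38.8, rounded up to 39.

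The stated 39 reproduces with one pair of test results per child. Nothing in it counts eyes.

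**2. Does a right/left term deal with the correlation?** Simulation: 39 children, two eyes each, an OCT-like outcome with inter-eye correlation ρ (assumed), and a child-level factor with no true effect, tested at a nominal 5%. Ordinary regressions used 1,000 runs. The random-intercept model, which also kept the eye term, used 400 runs and a Wald test.

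| Model | ρ = 0.5 | ρ = 0.8 |
|---|---|---|
| No eye term | 11.9% | 15.6% |
| Right/left term added | 11.7% | 15.5% |
| Right/left term plus random intercept for child | 7.0% | 5.5% |

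Monte Carlo standard errors are about 1 percentage point (√(0.119·0.881/1000) = 1.0; √(0.07·0.93/400) = 1.3). The right/left term changes nothing material. The child-level random intercept does most of the work.

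**3. What would follow if eyes were pooled as independent.** The protocol does not say that they will be. The documents give no inter-eye correlation, so ρ is an assumption, shown over 0.3–0.9.

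From the feasibility figures, 76% of children are bilateral and 86 − 76 = 10% unilateral.
- Mean eyes per imaged child: (2·0.76 + 0.10)/0.86 = 1.88.
- Size-weighted cluster size: (4·0.76 + 0.10)/(2·0.76 + 0.10) = 1.94.
- Design effect: 1 + 0.94ρ with this mix, or 1 + ρ if every child gives two eyes.
- Standard-error ratio: the square root of the design effect.
- Coverage of a nominal 95% interval: 2Φ(1.96/ratio) − 1.

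| ρ | Design effect (mix) | SE ratio | Coverage | Design effect (two eyes) | SE ratio | Coverage |
|---|---|---|---|---|---|---|
| 0.3 | 1.28 | 1.13 | 92% | 1.30 | 1.14 | 91% |
| 0.6 | 1.56 | 1.25 | 88% | 1.60 | 1.26 | 88% |
| 0.9 | 1.84 | 1.36 | 85% | 1.90 | 1.38 | 84% |

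**4. On the scale of sensitivity.** Take 62% sensitivity and, for illustration, all 39 children with IH and two eyes each (78 eyes).
- Pooled half-width: 1.96·√(0.62·0.38/78) = 10.8 points.
- Allowing for clustering: 10.8·√1.3 = 12.3 points at ρ 0.3, and 10.8·√1.9 = 14.8 points at ρ 0.9. The pooled interval is 12% to 27% too narrow.
- One result per child: 1.96·√(0.62·0.38/39) = 15.2 points, with nothing to correct.

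Fewer children with IH would widen every interval and leave the relative narrowing as it is.

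**The case against.** The strongest reply is that the sentence sits inside a mixed model. Such a model contains a random effect, and child is the natural grouping factor for paired eyes. The ICP assessment section also speaks of multilevel analyses. On that reading the child effect is intended and merely unnamed, and the table in step 2 shows that such a model largely works. This stands as far as it goes: a child effect is not excluded. It does not rescue the sentence, which credits the laterality term with the job.

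A reader might infer that the primary accuracy analysis is at eye level and that its intervals will therefore be too narrow. The documents do not support this. No section gives an eye-level unit for the primary analysis. The sample size is in children and fits a per-child analysis, where the problem does not arise. The article describes no interval method for sensitivity, specificity or AUC, and a full protocol or SAP that is not shown may settle the unit, so its absence here is not an error.

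The size is also soft, for three reasons.
- For sensitivity, the relevant correlation is that of the dichotomised result among children with IH. In the simulation, latent correlations of 0.5 and 0.8 became 0.33 and 0.58 after dichotomising, and the pooled interval covered 91.5% and 88.2%.
- For a predictor that varies by eye, such as eye-specific acuity, the inflation depends roughly on the product of two correlations. With both at 0.6 the design effect is 1 + 0.94·0.36 = 1.34 and the ratio 1.16, not 1.25.
- The bilateral rate comes from a craniosynostosis feasibility cohort, not from children undergoing ICP monitoring.

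**Conclusion.** The point holds as a wrong stated rule. Entering right/left eye does not address inter-eye correlation, and the child-level grouping that would do so is not named. The sentence governs the secondary-outcome associations only.

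For the primary accuracy and ROC analysis, the consequence is conditional on eyes being pooled as independent. In that case standard errors would need to be 25–36% larger at an assumed correlation of 0.6–0.9. Over 0.3–0.9 the range is 13–36% with the feasibility mix, or 14–38% if every child gives two eyes. Nominal 95% intervals would cover roughly 84–92% across these cases. The required 39 children are unaffected. What makes the point worth acting on is that the stated rationale is wrong and would carry into any analysis plan that repeats it.

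**What to change.** 1. In the mixed models, specify a random intercept for child, with eyes nested in child. Keep right/left only as a fixed covariate, and delete the statement that it addresses inter-eye correlation.
2. Make the child the unit of the primary accuracy and ROC analysis. Both eyes share one ICP result and the sample size counts children, so use one OCT value per child under a rule fixed before the data are seen. The mean of the analysable eyes is one example; a child with one analysable eye would then contribute that eye's value.
3. If any accuracy measure or AUC is also reported by eye, take its interval from a bootstrap that resamples children.

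The cost is a few sentences of analysis text, with no extra children or scans. The downside is somewhat wider intervals than pooling eyes would give: in the illustration, 15.2 points either side for one value per child against an apparent 10.8. Fixing the rule in advance also removes the choice of eye or unit after the results are known.
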